#### Outline of exploratory analysis of the temperature variables and time to death

Assuming that the temperature is measured at the same times relative to the time of the start of intervention, a mixed model may be used to characterise the time course of those patients who do not die during the treatment. The model is given by temperature = INT time time*INT, where INT is the intervention indicator. Additionally, the time to death from start of treatment with censoring at end of treatment and at 91 days +/-14 days including baseline variables measured at or prior to start of treatment may be analysed using a Cox proportional hazards model. The mean values of all the actual measured temperatures in the intervention group will be displayed in a graph with mean +/- 2 standard errors.

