## Introduction

The EuroHYP-1 trial is a multicentre, randomised, superiority phase III international clinical trial with masked outcome assessment testing the benefits and harms of therapeutic cooling in awake adult patients with acute ischaemic stroke (website: http://www.eurohyp1.eu). The trial is designed according to the SPIRIT guidelines, and the background, design, and rationale have previously been published [1]. The EuroHYP-1 trial protocol has been available online on www.ClinicalTrials.gov since the start of the trial on 4 April 2013. The trial is endorsed and supported by European Clinical Research Infrastructures Network (ECRIN) (www.ecrin.org).

Here we describe the updated detailed statistical analysis plan that has been finalised while data collection in the EuroHYP-1 trial is underway, and to which all data analyses in the main publication of the EuroHYP-1 trial results will adhere. A detailed statistical analysis plan was part of the protocol, and the Steering Group of the EuroHYP-1 trial unanimously approved the statistical analysis plan on 30 March 2016. The present amendments of the original statistical analysis plan focus on the primary and the secondary outcomes. The amendments have been made in order to make the analysis more concrete and transparent. Patient recruitment of 800 patients is expected to be completed, and the final follow-up is predicted to occur in 2018–19, after which the database will be locked and data will be analysed.

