**Fig. 1 Fig1:**
[figure not shown]
Overview of patient schedule and data collection in the EuroHYP-1 trial (*grey tone* only for the experimental group). 1 Re-warming: hypothermia group only. 2 Previous medication including alteplase. 3 Includes sodium, potassium, magnesium, creatinine, urea, gamma-glutamyl transpeptidase, ASAT, ALAT, alkaline phosphatase, blood glucose; haemoglobin, haematocrit, erythrocytes, leukocytes, platelets, INR. Further samples may be taken throughout the study at the discretion of the investigator. 4 Body temperature will be assessed according to local clinical practice with tympanic, bladder, or rectal temperature measurement, except in patients randomised to therapeutic hypothermia from start of treatment phase (TP, beginning of hour 1) until end of re-warming period, when bladder or rectal thermal probes will be used. During TP, body temperature will be assessed every 15 min during the first 3 hours (except at time points t = 0 min and t = 15 min) and every 60 min thereafter in patients randomised to therapeutic hypothermia, every 60 min (except at time point t = 0 min) in patients randomised to best medical treatment alone, subsequently in all patients at 8-hour intervals until A6 (day 8 or day of discharge from hospital, whichever occurs first). 5 The mRS assessment at outcome assessment (A7) will be recorded using a digital video camera. The clip will then be transferred to the EuroHYP-1 outcome adjudication web portal. 6 Anti-shivering medication: induction: buspirone 10 mg p.o./pethidine 50 mg i.v. (2 min); repeat doses of 10 mg buspirone p.o. may be administered as long as a maximum dose of 30 mg/24 h is respected; a bolus of pethidine 25 mg i.v. may be given as long as an interval of at least 30 min is respected and a maximum dose of 500 mg/24 h is not exceeded. 24 h-doses include induction bolus. For the prevention and treatment of opioid-induced nausea and vomiting, a 5HT3RA may be administered as support medication. 7 Induction of cooling: 20 ml/kg estimated bodyweight 4 °C isotone saline or Ringer´s lactate over a period of 30–60 min; EMCOOLS Brain.Pad, if available. 8 IMDs permitted for cooling: EMCOOLS Brain.Pad (for induction of cooling only); Medivance/Bard Arctic Sun temperature management system with heat exchange control unit Arctic Sun 2000 or Arctic Sun 5000 and ArcticGel Pads; MTRE CritiCool temperature management system with heat exchange control unit CritiCool, accessoires and CureWrap; Zoll IVTM system with heat exchange control unit CoolGard 3000 or Thermogard XP, CoolGard start-up kit and intravascular temperature management catheters ICYy 3893 AE or ICY 3893 CO. 9 If endovascular cooling is performed, the catheter insertion site must be visually inspected for detection of bleeding/haematoma in 3-hour intervals during TP and once 3 hours after removal of the intravascular catheter. 10 Monitoring for pneumonia includes monitoring of oxygen saturation and body temperature, physical examination (auscultation, percussion) and, if clinically indicated, chest X-ray. Monitoring for signs of pneumonia must be performed from screening assessment (A1, within 90 minutes before the start of the treatment phase TP) until A6 (day 8 or day of discharge from hospital, whichever occurs first). 11 Patient location during stay in hospital must be assessed at 12:00 hours on each day in hospital. 12 WHODAS 2.0 questionnaire and EQ-5D questionnaire must be filled in by the patient or his/her relative/carer at outcome assessment (A7). 13 Health Recovery Guide and Diary: Section 6: filled in by the patient every day from discharge to V7; Section 7: filled in by the carer/relative prior to V7. 14 For participation in the biomarker sub-study a special informed consent form must be filled in by the patient or his/her legal representative. Assessment at End of Hour 24 ± 2 hours. 15 Only selected study sites. 16 Informed consent will be obtained in accordance with national regulatory requirements. 17 NIHSS assessment at End of Hour 24 ± 2 hours. 18 Starting at t = 30 min. 19 Every 60 minutes only. 20 Prior to intended repeat administration of pethidine. *CT* computed tomography, *ECG* electrocardiogram, *EQ-5D-5 L* EuroQoL quality-of-life scale, GCS Glasgow coma scale, *MRI* magnetic resonance imaging, *NIHSS* National Institutes of Health Stroke Score, *SAE* serious adverse event, *WHODAS* World Health Organization Disability Assessment Schedule

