### Adjusting variables

The randomisation is stratified according to the nationality of the participating centres and, within each stratum, the patient allocation is based on probabilistic minimisation (80:20) using the following factors:Intention to perform thrombolysis (yes compared to no).Method of cooling (surface compared to endovascular).Sex (male compared to female).Stroke severity (National Institutes of Health Stroke Score (NIHSS)) 6–12 compared to 13 or higher).Age (≤ 65 years compared to > 65 years).Visibility of a relevant ischaemic lesion on the first brain imaging (yes compared to no).Time since symptom onset (≤ 4 hours compared to 4–6 hours).

The primary analyses will be adjusted by the protocol-specified stratification variable country and the seven minimisation factors.

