#### Subgroup analysis

The duration of the cooling intervention was reduced from 24 hours to 12 hours after the recruitment of 50 participants. To investigate this protocol change, we will conduct a subgroup analysis for the primary and secondary outcomes. In the analysis, we will compare the participants who were included before the protocol change to participants included after the protocol change.

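### The exploratory temperature graph and mixed model make no distinction between participants cooled for 24 hours and for 12 hours, so anything shown after hour 12 mixes two regimens.

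*SAP article*

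**What the plan says.** The section outlining the exploratory temperature analysis makes one firm commitment, the graph: "The mean values of all the actual measured temperatures in the intervention group will be displayed in a graph", with bars of two standard errors. It also offers a mixed model as an option. That model starts from a premise about timing, "Assuming that the temperature is measured at the same times relative to the time of the start of intervention", and its terms are listed in full: "The model is given by temperature = INT time time*INT, where INT is the intervention indicator". Cooling duration and protocol version appear in neither, and no time span is given for either.

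The Subgroup analysis section reports the change of regimen: "The duration of the cooling intervention was reduced from 24 hours to 12 hours after the recruitment of 50 participants". It then plans a comparison of participants enrolled before and after the change, but only for the primary and secondary outcomes. Temperature is neither.

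Note 4 to Fig. 1 gives the reading schedule. During the treatment phase, cooled patients are read every 15 minutes for three hours "and every 60 min thereafter in patients randomised to therapeutic hypothermia". After that phase, readings continue "subsequently in all patients at 8-hour intervals until A6", that is, to day 8 or discharge.

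**The concern.** A change in cooling duration alters the temperature course more directly than any other variable. The article treats the change as important enough to examine in every primary and secondary outcome, yet not in the temperature analysis. Between hours 13 and 24 an early cooled participant is meant to be still cold, while a later one has finished cooling. An average of the two describes neither regimen.

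The number of readings may differ as well as the level. If dense readings stop when cooling stops, early participants contribute hourly values in hours 13-24 and later ones only occasional values. The set of people behind each plotted mean would then change from one time point to the next, and the standard-error bars with it.

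At stake is how readers judge the cooling delivered. The graph could suggest longer cooling or slower re-warming than participants on the 12-hour regimen had. The table of amendments says the temperature work is meant to assess whether temperature affects mortality, so the description should be sound even though nothing is formally tested on it.

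**Working it through.** The plan gives no figure of its own on this point, so there is nothing to reproduce. The check is how much weight the early participants carry after hour 12.

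**Inputs from the article**
- Planned total 800 (Introduction).
- Participants enrolled before the change: 50, both arms together (Subgroup analysis).
- Readings hourly after the first three hours of the treatment phase in cooled patients, and 8-hourly in everyone once that phase ends (Fig. 1, note 4).

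**Assumptions**
- Allocation 1:1. The 80:20 in Adjusting variables is the minimisation probability, not an allocation ratio, and no ratio is stated in the text shown.
- 24-hour participants were read hourly through hour 24. Their schedule is not shown.

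**Share of patients**
- Cooled arm: 800/2 = 400. Early cooled: 50/2 = 25. Later cooled: 400 - 25 = 375.
- Early share: 25/400 = 6.25%.

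**Share of readings in hours 13-24**

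With 12 readings per early patient and k per later patient, the early share is 25 × 12 / (25 × 12 + 375 × k) = 300 / (300 + 375k).

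| Later patients read after hour 12 | k | Early share |
|---|---|---|
| Hourly to hour 24 | 12 | 300/4800 = 6.25% |
| Hourly for 6 h, then 8-hourly | 6 + 6/8 = 6.75 | 300/2831.25 = 10.6% |
| 8-hourly, spread evenly over the hours | 12/8 = 1.5 | 300/862.5 = 34.8% |
| 8-hourly on one common grid (one reading, at hour 20) | 1 | 300/675 = 44.4% |

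**Share at single time points**
- Readings spread evenly: each hour has 25 early and 375/8 = 46.9 later readings, so the early share is 25/71.9 = 34.8%.
- Common grid: at hour 20 the early share is 25/400 = 6.25%. The other 11 of the 12 hourly points contain early patients only.
- After hour 24, with everyone 8-hourly: 6.25%.

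**Effect on a plotted mean**

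At a given time, the pooled mean differs from the 12-hour participants' mean by the early share times the temperature gap between the two groups. Per 1 °C of gap that is 0.06 °C at a share of 6.25% and 0.35 °C at 34.8%. The text shown gives no re-warming rate, so the gap cannot be filled in.

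**The case against.** **The stronger reading.** A reader might infer that after hour 12 the curve is dominated by, or consists entirely of, the early 24-hour participants. The article does not support that. Later participants go on being read 8-hourly to day 8 or discharge. At 800 patients, the early group is a minority of readings in hours 13-24 in every scenario above and 6.25% after hour 24. Points with early participants only arise on a strict common grid. A majority of readings would need enrolment well short of target: under even spreading, 300/(300 + 175 × 1.5) = 53% at 400 patients in total. A definite bias in degrees cannot be claimed either, since it would rest on an assumed re-warming rate.

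**What is not shown.** Fig. 1 is missing from the text available. The notes keep bladder or rectal probes in use in cooled patients until re-warming ends, so closer readings then are possible. With hourly readings to hour 24 in both versions, the early share is only 6.25%. The graph and model might also stop at hour 12, and the problem would then not arise. The model is optional and conditional on common measurement times. All this stands and limits the size of the point. It does not supply the missing split, and the graph is a firm commitment without that condition.

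**Other records of cooling.** The per protocol definition captures whether 35.0 °C or below was reached within 3 hours and held for at least 6 of the first 12 hours. The graph is therefore not the article's only account of the cooling achieved. That also stands.

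**Consequence.** The analysis is labelled exploratory and lies outside the fixed testing sequence, and a condensed article may leave plotting detail elsewhere. This is fair on importance. However, the article lists the model terms in full and says which outcomes the before/after comparison covers.

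**Conclusion.** The point holds in a limited form. As written, the temperature graph and model pool two cooling durations with no split or term for duration, and the planned before/after comparison does not reach temperature. If either extends past hour 12, it mixes participants being cooled with participants re-warming.

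Under 1:1 allocation and 800 patients, about 25 early cooled participants supply between 6.25% and about 44% of readings in hours 13-24. The low end applies if both versions were read hourly, and about 35-44% if later participants were read 8-hourly. On a strict common grid, some hourly points could rest on early participants alone. Which case applies depends on schedules and a time span that are not shown, so the distortion cannot be fixed in size. No confirmatory result is affected. This is a low-cost improvement to a descriptive analysis.

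**What to change.** In the section on the temperature variables:
- Plot cooled-arm means separately for participants randomised before and after the duration change, using the same division as the Subgroup analysis section, and print the number contributing at each time point.
- Either restrict the pooled graph and mixed model to hours 0-12, which both versions share, or add protocol version to the model with its interactions with time and intervention. The three-way term matters most, because the change in duration acts only in the cooled arm.
- Describe hours 13 onward by version only, and state the time span of the graph and model.

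The cost is a few sentences of SAP wording and one stratified plot from data already collected. The drawback is that the early-version curve rests on about 25 patients and will have wide error bars. The same small number would make the version interactions imprecise, so restricting to hours 0-12 is the simpler choice for the model.

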#### Health economic evaluation

The economic assessments will be conducted in alignment with the Consolidated Health Economic Evaluation Reporting Standards (CHEERS) statement [13]. The prospective analysis will determine the cost per QALY gained with systemic cooling compared with standard care over a 3-month period. Acute hospital post-discharge resources will be considered in the evaluation. Procedural costs for systemic cooling will be obtained with a bottom-up micro-costing approach in order to identify all relevant cost components of the procedure and value each component for all individual patients, using procedure duration, staff, and number of medical devices as variables. All-cause hospital admissions within 3 months of the first treatment will also be included in cost computations. Non-hospital resources are not considered in view of the short follow-up duration.

Cost of systemic cooling will be the manufacturer’s price, and staff costs will be estimated from gross salaries. Hospital inpatient costs will be estimated using current average national cost of each patient’s diagnosis-related group (DRG), adjusted for actual length of stay, and resources consumed during hospitalisation. Hospital re-admissions will be based on tariffs. All costs will be in Euros (€) and are not discounted. Health-related quality of life collected using the EQ-5D-5 L self-administered questionnaire at baseline and 3 months will be used to elicit utility values based on country-specific tariffs. The difference in QALYs will be estimated as the difference in the area between the utility curves for the two groups.

We will undertake a fully pooled analysis for clinical outcomes and a country-specific analysis for costs (based on the countries with the highest patient volume) [14].

The cost-utility analysis will estimate incremental costs per QALY and the cost-effectiveness incremental cost per death or disability (as defined in the secondary outcomes) averted. Between-group comparisons of QALYs and costs will be performed with the statistical test appropriate for their distribution, with a significance threshold of 0.05. A joint comparison of costs and effects will be performed by nonparametric bootstrapping with 1000 resamples and the result of the bootstrap replications presented on the cost-effectiveness plane (scatterplot).

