### Statistical analyses

#### Analytical principles

Analyses will be conducted according to the intention-to-treat principle [2] if not otherwise stated.

All primary tests of significance will be two-sided with alpha = 5%. Analyses will be conducted blinded with the two intervention groups coded as, e.g. 0 and 1. Two conclusions will be drawn, one assuming 0 is the intervention group and 1 is the control, and one assuming the opposite. After two abstracts with two conclusions have been written and both accepted by the Steering Group, the code will be broken.

The primary analyses of primary, secondary, and exploratory outcomes will be those of the intention-to-treat population adjusted for the protocol-specified stratification variable and the minimisation variables, and if necessary using data sets generated using multiple imputation.

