#### Power of the original secondary outcomes

As the sample size is based on the primary outcome, we have calculated the power of each of the originally planned secondary outcomes given the sample size of 800 patients.

Death day 91 ± 14 days after randomisation: the implied clinically relevant minimal change in mortality that needs to be detected may be calculated based on (1) the mortality of 17% found in the meta-analysis quoted in the protocol [1]; (2) the assumption that wherever the mRS is dichotomised, the odds ratio for treatment versus control will be the same, the ‘common odds ratio’; and (3) the requirement that this common odds ratio should not be larger than 0.74 (see the sample size calculation). Let the unknown change in mortality in the experimental group be x. If we assume the OR for the dichotomy mRS > 5 compared to mRS ≤ 5 will be 0.74 and the mortality of the control group is 17% as quoted in the meta-analysis, we may find x by solving the equation OR = ((0.17–x)/(0.83 + x))/(0.17/0.83) = 0.74 to obtain x = 0.0384 giving a mortality of 0.1700 – 0.0384 = 0.1316 in the cooled patients versus 0.1700 in the controls. Using a sample size of 800 participants, the power is found to be 0.33.

Death or dependency (mRS > 2) 91 ± 14 days after randomisation: using the same reasoning, the power of this outcome can be calculated by solving the equation (0.63–x)/(0.37 + x))/0.63/0.37 = (0.63 – x)0.63/(0.37 + x)0.37 = 0.74 as 63% of the patients in the meta-analysis had mRS > 2 implying x = 0.0725. The power may then be calculated to be 0.55.

NIHSS score 91 ± 14 days after randomisation: assuming a minimal relevant difference of 2 points, a standard deviation (SD) of 5 points [5], an α of 0.05, and a sample size of 800 participants, the power may then be calculated to 1.00.

EQ-5D-5 L score 91 ± 14 days after randomisation: assuming a minimal relevant difference of 0.05 points, a SD of 0.40 points [6–9], an α of 0.05, and a sample size of 800 participants, the power may then be calculated to 0.42.

WHODAS 2.0 score 91 ± 14 days after randomisation: we originally planned to analyse the World Health Organization Disability Assessment Schedule II (WHODAS 2.0) score at outcome assessment in the period day 91 ± 14 days after randomisation. However, due to difficulties in assessing the clinical meaning, we are not able to calculate the power, and we will thus analyse this as an exploratory outcome.

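### Incremental QALYs are the difference in area under the utility curves with no adjustment for baseline EQ-5D-5 L, so chance baseline imbalance enters the estimate and precision is lost

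*SAP article*

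**What the plan says.** Under Health economic evaluation, the SAP article sets out a "cost per QALY gained with systemic cooling compared with standard care over a 3-month period". The utilities come from two time points: "Health-related quality of life collected using the EQ-5D-5 L self-administered questionnaire at baseline and 3 months will be used to elicit utility values". The estimator is then stated: "The difference in QALYs will be estimated as the difference in the area between the utility curves for the two groups". Testing is left open: "Between-group comparisons of QALYs and costs will be performed with the statistical test appropriate for their distribution, with a significance threshold of 0.05". For the cost-effectiveness plane, "A joint comparison of costs and effects will be performed by nonparametric bootstrapping with 1000 resamples".

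Three places bear on adjustment:

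- The abstract says that all analyses are adjusted for nationality of centre and the minimisation variables.
- Adjusting variables lists country and seven factors: thrombolysis intention, cooling method, sex, NIHSS band, age band, visible lesion and time since onset.
- Analytical principles is narrower: "The primary analyses of primary, secondary, and exploratory outcomes will be those of the intention-to-treat population adjusted for the protocol-specified stratification variable and the minimisation" (the sentence continues). The health-economic outcome is listed separately from those outcome classes.

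Baseline EQ-5D-5 L appears in none of them.

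Two further places matter. Fig. 1 note 12 requires the EQ-5D questionnaire at the outcome assessment (A7) and mentions no baseline completion. The Discussion section on outcomes measurable only in survivors sets QALYs to zero from death onwards.

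**The concern.** With only two utility measurements, the baseline value makes up half of a survivor's area. Cooling cannot change a value recorded before treatment, so any chance difference between the arms in baseline utility is counted as QALYs gained or lost. Baseline utility may also predict the day-91 value, and leaving it out leaves explainable variance in the standard error.

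The incremental QALY is the denominator of the cost-utility ratio and one axis of the cost-effectiveness plane. Over three months the expected gain is very small, so a modest absolute shift is a large relative one. The bootstrap cloud is also wider than the data would require.

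**Working it through.** **Inputs from the SAP article.** Day-91 difference and SD: "assuming a minimal relevant difference of 0.05 points, a SD of 0.40 points". Sample size and stated power: "a sample size of 800 participants, the power may then be calculated to 0.42". Two-sided alpha 5%. Control mortality 17%.

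**Assumptions not in the article.** 400 per arm; linear interpolation between the two measurements; baseline SD s0 from 0.10 to 0.40; correlation rho between baseline and day-91 utility from 0 to 0.7. Steps 1 to 5 ignore deaths and minimisation.

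**1. The plan's own figure.** Two-sample comparison, difference 0.05, SD 0.40, 400 per arm: power 0.424, against the stated 0.42. It reproduces.

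**2. Expected QALY gain.** T = 91/365.25 = 0.249 year. A survivor's QALY is (T/2)(u0 + u91), with T/2 = 0.1246, or about 0.125. A 0.05 difference at day 91 and none at baseline gives 0.1246 × 0.05 = 0.0062 QALY.

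**3. Direct effect of baseline imbalance.** A baseline difference d adds 0.125 × d, which is d/0.05 of the expected gain. For d = 0.02 this is 0.0025 QALY, or 40%. One standard error of d under simple randomisation is s0 × sqrt(2/400):

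| s0 | one SE of d | QALY shift | share of 0.0062 |
|---|---|---|---|
| 0.10 | 0.0071 | 0.0009 | 14% |
| 0.20 | 0.0141 | 0.0018 | 28% |
| 0.40 | 0.0283 | 0.0035 | 57% |

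**4. Precision.** With s1 = 0.40, the per-patient variance is:

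- unadjusted: (T/2)² × (s0² + s1² + 2 × rho × s0 × s1)
- adjusted for u0: (T/2)² × s1² × (1 − rho²)

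| s0, rho | SE unadjusted | SE adjusted | variance ratio | power unadjusted | power adjusted |
|---|---|---|---|---|---|
| 0.10, 0 | 0.0036 | 0.0035 | 0.94 | 0.40 | 0.42 |
| 0.10, 0.3 | 0.0039 | 0.0034 | 0.75 | 0.36 | 0.46 |
| 0.20, 0.3 | 0.0044 | 0.0034 | 0.59 | 0.30 | 0.46 |
| 0.40, 0.3 | 0.0057 | 0.0034 | 0.35 | 0.19 | 0.46 |
| 0.40, 0.5 | 0.0061 | 0.0031 | 0.25 | 0.17 | 0.53 |

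**5. Simulation check.** In 3000 trials per setting, both estimators averaged close to 0.0062, so both are unbiased. The unadjusted estimate moved with the baseline difference by 0.16 to 0.20 QALY per unit. This is above 0.125 because baseline also predicts day 91. The adjusted slope was about 0.

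**6. Deaths.** A simulation with 17% mortality and zero utility after death, with death times and mean utilities assumed, shrinks the gain but does not remove it. The variance ratio is roughly 0.5 to 0.75 for s0 0.20 to 0.40 and rho 0.3 to 0.5, and 0.97 in the least favourable case (s0 0.10, rho 0).

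**The case against.** **Is baseline utility collected at all?** Fig. 1 note 12 mentions EQ-5D only at A7. If there is no patient-level baseline, or every patient is given one common value, u0 has no spread: nothing is lost and the covariate cannot be fitted. This objection stands as a condition on the remedy. It does not rescue the present text, because the planned area needs the same baseline value.

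**The economic analysis is only outlined.** The Discussion leaves the detailed economic quantities to separate publications, and a test suited to the distribution excludes no model. A fuller economic plan could add the covariate. But this article states its estimator outright, and neither remark withdraws it.

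**General adjustment may already apply.** A reader might infer that QALYs are planned with no adjustment whatever. The documents do not settle that: the abstract speaks of all analyses, while Analytical principles names three outcome classes that do not include this one. On either reading baseline utility is absent. If the abstract governs, part of the gain in step 4 is already secured.

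**The sizes are upper-end.** Minimisation on NIHSS band, age and the other factors reduces baseline imbalance so far as they predict utility, and deaths reduce the weight of baseline. Both points stand, and the figures should be read that way.

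**Bias or reversal.** A reader might also infer that the planned estimate is biased, or that ordinary imbalance reverses its sign. Neither is supported. The estimator is unbiased over randomisation, and a one-standard-error imbalance acting directly through the baseline half reaches at most 57% of the expected gain in the range examined.

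**Conclusion.** The point holds as a matter of precision and of chance error in this one trial. The stated QALY estimator leaves out baseline utility, and no adjustment rule in the article supplies it.

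Its size is uncertain because baseline SD and correlation are not given. With little baseline spread and no correlation, adjustment gains almost nothing (power 0.40 to 0.42). With baseline SD 0.20 and rho 0.3 the gain is useful (0.30 to 0.46). The rise from 0.17 to 0.53 belongs to the large-spread case, SD 0.40 and rho 0.5, and should not be taken as the expected benefit. All these figures assume linear interpolation and 400 per arm, and they fall once deaths, minimisation and any covariate adjustment already intended are allowed for.

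The primary outcome and the fixed testing sequence are unaffected. The consequence is confined to the cost-utility ratio and the cost-effectiveness plane.

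**What to change.** First, reconcile Fig. 1 note 12 with Health economic evaluation, stating whether EQ-5D-5 L is recorded for each patient at baseline and how.

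Provided it is, replace the estimator sentence in Health economic evaluation with wording such as: *The difference in mean QALYs will be estimated by linear regression of each patient's QALY (zero utility from death onwards) on intervention group, baseline EQ-5D-5 L utility, country and the minimisation factors. The same model will be refitted in each of the 1000 bootstrap resamples. The unadjusted difference will be shown as a supplementary result.*

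The cost is a short text change and a regression step inside a bootstrap that is already planned. No further data are needed if the baseline questionnaire is collected as that section says; whether it is depends on the reconciliation. Missing baseline utilities will need imputation, but the unadjusted area needs those values too. Settling the wording before data lock also removes a later choice between unadjusted and adjusted results.
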